## **5.4 Analytical Plan**

Descriptive statistics will be generated for all baseline patient characteristics, complications, and endpoints. Frequency counts and percentages will be used to summarize binary and categorical data. Continuous data will be summarized using means  $\pm$  standard deviation, median and interquartile range, and minimum/maximum values. ANOVA tests will be used to describe the difference in number of days to a 50% reduction on the symptom severity score between the four groups. All pairwise comparisons will be generated and adjusted for multiple comparisons using the Tukey method.

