| Design             | A prospective, open label four arm study (1. Zinc only 2. Zinc and ascorbic acid 3. Ascorbic acid only 4. Standard of care. All subjects will receive the supplements for 10 days after positive test result                                                                                                                                                                                                                                                                                                                                                                                                                                                                                                                                                                                                                                                                                                                                                                          |
| Number of Subjects | 520                                                                                                                                                                                                                                                                                                                                                                                                                                                                                                                                                                                                                                                                                                                                                                                                                                                                                                                                                                                   |

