## **2.0 Study Design, Objective, and Clinical Endpoints**

This is a prospective, randomized study which plans to enroll 520 patients with a principal diagnosis of COVID-2019, managed in an outpatient setting, who presented after being sent by a healthcare provider to get tested and receive a PCR-assay based confirmed diagnosis of the disease. All patients who agree to participate in the study will answer a baseline questionnaire about their symptoms at the time of inclusion. Patients will then be randomized to one of 4 study arms. Patients in Arm A (n=130) will receive 8000 mg of vitamin C (to be taken divided over 2-3 times a day with meals) for 10 days after positive diagnosis. Patients in Arm B (n=130) will receive zinc gluconate 50 mg for 10 days, to be taken at bedtime, after positive diagnosis. Patients in Arm C (n=130) will receive 8000 mg of vitamin C (to be taken divided over 2-3 times a day with meals) and zinc gluconate 50 mg for 10 days (taken at bedtime). Patients in Arm D (n=130) will not receive any of the study medications and continue on standard of care.

Patients will then track their symptoms daily from day 0 to day 28 answering 12 basic questions on illness severity. Symptom assessment tools will be completed by patients daily either electronically or on paper. For those completing the tool electronically a tool will be emailed to the patient daily via RedCap. For those completing the tool on paper a 28 day paper assessment tool will be provided to the patient at the time of consent via email/courier/text/express mail. For those patients completing a paper tool, a research staff member will contact the patient daily via phone call to obtain their daily assessment scores. Study team members will call patients at days 7, 14, 21, and day 28 of the study period to obtain information regarding hospitalizations, ER visits, additional medications prescribed by a healthcare provider

or over the counter, and any side effects from the study supplements that the patient could have experienced. Study team members may also call patients if non-compliance with completion of the daily symptom assessment tool.

Patients seen in the Emergency Department (ER) during the course of study participation will continue to take study supplement(s) (if within the initial 10 days) and continue daily symptom assessments as above.

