## 232 **5.0 Statistical Analysis and Endpoints**

### 233 **5.1 Sample Size:**

234 This randomized control trial will aim to prospectively enroll 520 patients who have  
 235 received a positive confirmed diagnosis of coronavirus 2019. All patients will be followed for 28  
 236 days to review vital status, hospitalizations, emergency room visits, and need for additional  
 237 treatment. We assumed the standard of care group will have a 50% reduction of symptom  
 238 severity in approximately  $6 \pm 3$  days, and that at least one of the other 3 study groups will reach a  
 239 50% reduction in  $5 \pm 3$  days. When the sample size in each of the 4 groups is 130, a one-way  
 240 analysis of variance will have 80% power (2-sided alpha of 0.05) to detect a difference in means  
 241 characterized by a variance of means, V, of 0.188, assuming that the common standard deviation  
 242 is 3 days. Our study aims to enroll 520 patients to account for study drop out as well.

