### 243 **5.2 Primary Endpoints**

244 The primary endpoint will be the number of days required to reach a 50% reduction in the  
 245 symptom severity score from peak symptom score.

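### Section 5.4 fixes an unadjusted ANOVA although a baseline symptom score is available, and 5.1 leaves unstated that a single supplement-versus-control pair has about 54% power under Tukey

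*Protocol*

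**What the plan says.** The design has four arms: "1. Zinc only 2. Zinc and ascorbic acid 3. Ascorbic acid only 4. Standard of care" (Study Synopsis, Design). Section 2.0 allocates 130 patients to each.

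Section 5.2 defines the primary endpoint as the time from the peak symptom score to a halving of that score.

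Section 5.1 powers the trial on the omnibus test: the one-way "analysis of variance will have 80% power (2-sided alpha of 0.05) to detect a difference in means" described by V = 0.188 and a common SD of 3 days. The scenario behind V is 6 days on standard of care and that "at least one of the other 3 study groups will reach a" 50% reduction in 5 days.

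Section 5.4 names ANOVA for the four-group comparison, with no covariate, and continues: "All pairwise comparisons will be generated and adjusted for multiple comparisons using the Tukey method". No power is given for any pair.

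On baseline data, section 2.0 says: "All patients who agree to participate in the study will answer a baseline questionnaire". The questionnaire concerns symptoms at inclusion, and randomisation follows it. The schedule in 4.1 also marks symptoms at screening/baseline.

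**The concern.** There are two linked issues.

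First, a significant omnibus F test says only that the four means are not all equal. Whether a particular supplement shortens symptoms relative to standard of care is answered by the pairwise tests. Section 5.1 describes its scenario in terms of a supplement arm against standard of care but gives power only for the F test. A reader could take the 80% as the chance of showing that a given supplement works.

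Second, 5.4 tests the raw group means. A symptom score is collected from every patient before randomisation, and using it as a covariate removes whatever part of the outcome variance it explains. Leaving it out forgoes precision in a trial where the comparison of most interest has limited power.

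**Working it through.** **Inputs**
- n = 130 per arm, four arms (2.0, 5.1).
- SD = 3 days and two-sided alpha = 0.05 (5.1).
- Means of 6 days on standard of care and 5 days in at least one supplement arm, so the difference is 1 day (5.1).
- V = 0.188 (5.1). It matches the variance of 6, 5, 6, 6 with divisor 4: the mean is 5.75, and (3 × 0.25² + 0.75²)/4 = 0.1875.
- All six pairs by Tukey (5.4).
- The correlation rho between baseline total score and endpoint is not in the protocol. It is assumed at 0, 0.2, 0.3 and 0.5.

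**Step 1: the plan's own figure.** The omnibus F test has 3 and 516 degrees of freedom and noncentrality 4 × 130 × V / 9.
- V = 0.188: noncentrality 10.86, power 79.5%.
- V = 0.1875: noncentrality 10.83, power 79.4%.

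The stated 80% is reproduced.

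**Step 2: one supplement-versus-control pair under Tukey.**
- Standard error = 3 × sqrt(2/130) = 0.372.
- Noncentrality = 1/0.372 = 2.687.
- Critical value = q(0.95; 4, 516)/sqrt(2) = 3.645/1.414 = 2.577.
- Power from the noncentral t with 516 df = 54.4%.

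**Step 3: how the two tests relate (simulation, SD 3, 130 per arm).**
- One arm at 5 days, the rest at 6: at least one supplement-versus-control pair passes Tukey in 55% of trials. In about 25% of trials the F test is significant but no such pair is.
- All three supplement arms at 5 days: at least one such pair passes in 79% of trials.

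**Step 4: baseline score as covariate.** The residual SD is 3 × sqrt(1 − rho²), and one degree of freedom is spent (516 becomes 515). V = 0.1875 for the F test.

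| Assumed rho | Residual SD | F-test power | Tukey power, one 1-day pair |
|---|---|---|---|
| 0 | 3.00 | 79.4% | 54.4% |
| 0.2 | 2.94 | 81.2% | 57% |
| 0.3 | 2.86 | 83.4% | 59% |
| 0.5 | 2.60 | 90.4% | 70% |

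At rho = 0 the lost degree of freedom does not change either figure at the precision shown.

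**Step 5: the alternatives, for scale.**
- Dunnett, three comparisons with standard of care: critical value about 2.355, power 63% for the same pair without a covariate.
- Factorial main effect (260 v 260): standard error = 3 × sqrt(2/260) = 0.263. A full 1-day marginal effect has noncentrality 3.80 and power 96.7%. If only one arm, or all three supplement arms, are at 5 days, the marginal effect is 0.5 day in size, the noncentrality is 1.90 and the power is 47.5%.

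**The case against.** The strongest reply is that nothing in 5.1 or 5.4 is wrong. The 80% is attached to the ANOVA, is correct for it, and no pairwise power is claimed. Tukey after a four-group ANOVA is valid, and the primary objective in 2.1 concerns all four arms. This stands. A reader might infer that the protocol promises 80% for each supplement against standard of care, but the text does not say so. Nor does 54% mean that the trial as a whole misses a real effect almost half the time. It applies to one named pair, and under either scenario in Step 3 Tukey flags at least one truly different pair about 79% of the time.

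A reader might also infer that Tukey should give way to Dunnett, or to the 2×2 factorial analysis, as a gain without cost. The documents do not support that:
- Dunnett adds about 9 points for the pair but makes contrasts between active arms, such as combination against single agent, descriptive. At 63% it is still below 80%.
- The 96.7% for a factorial main effect needs a full 1-day marginal effect, which the protocol does not assume. With one arm or all three at 5 days, both consistent with the protocol's V, the main effect has less power than the Tukey pair.

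On the covariate, two objections carry some weight. The endpoint is counted from the peak score, not from baseline, so the correlation may be small. Covariates are also often left to the statistical analysis plan, which is not shown. The first limits the size of the gain but creates no loss. The second would settle the matter if that plan adds the covariate, but 5.4 as written specifies ANOVA without one, and the two documents should agree.

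**Conclusion.** The point holds as an improvement to the analysis and a clarification of power, not as an error in the sample size. The 80% is right for the omnibus F test. The power for a single 1-day supplement-versus-control pair under the planned Tukey adjustment is about 54%, and the protocol should say so. Adjusting for the baseline total score would add between nothing and about 16 points to that pair (54% to 70%), and between nothing and about 11 points to the F test (79% to 90%), for assumed correlations from 0 to 0.5.

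These figures rest on the protocol's SD of 3, a true difference of 1 day, an endpoint observed as a continuous value in every patient, and all 130 patients per arm contributing. The size of the covariate gain depends on a correlation that the protocol does not give. That adjustment does no material harm does not depend on it.

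**What to change.** - **Section 5.4:** fit the four-group comparison and the Tukey-adjusted pairs from one linear model with treatment arm as factor and the baseline total symptom score as covariate. Define that score as the total reported before randomisation, on the same 12-symptom scale as the endpoint.
- **Section 5.1:** beside the omnibus 80%, add that a single 1-day supplement-versus-standard-of-care pair has about 54% power under Tukey without adjustment (SD 3, 130 per arm). If a gain from adjustment is quoted, state the assumed correlation.

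The cost is wording in two sections and one degree of freedom out of 516. No extra patients or assessments are needed, and all six Tukey comparisons stay.

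If the team regards the comparisons with standard of care as the main question, it may consider Dunnett, accepting that contrasts between active arms become descriptive. Factorial main effects with an interaction test could be added as supporting analyses, with the additivity assumption stated. Neither is required to resolve this point.

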## **6.0 Safety Reporting**

### **6.1 Definitions**

#### **6.1.1 Adverse Events**

An adverse event (AE) is any event, side effect, or untoward medical occurrence in a subject in a clinical trial whether or not it is considered to have a causal relationship to the study drug, device or procedure. An AE can therefore be any unfavorable and unintended sign, symptom, laboratory finding outside of normal range, physical examination finding, or disease

temporally associated with the use of the study drug, device or procedure whether or not the event is considered related to the study drug, device or procedure.

### 6.1.2 Serious Adverse Events

Adverse events are classified as serious or non-serious. A *serious adverse event* is defined as any adverse event occurring that results in any of the following outcomes:

- 1) Death
- 2) A life-threatening experience
- 3) Inpatient hospitalization
- 4) A persistent or significant disability or incapacity
- 5) A congenital anomaly or birth defect

Important medical events that may not result in death, be life-threatening, or require hospitalization may be considered a serious adverse event when, based upon appropriate medical judgment, they may jeopardize the patient or subject and may require medical or surgical intervention to prevent one of the outcomes listed in this definition.

### 6.1.3 Documenting and Reporting of Adverse Events

For the purposes of this study adverse events that are in the opinion of the investigator, thought to be both serious, unexpected and related to study supplement(s) or procedures should be recorded in the database and reported to the IRB per current reporting policies and procedures. All patient deaths; regardless of causality or relatedness should be recorded in the database and reported to the IRB as per current IRB reporting policies.

290 We will have a study safety committee to evaluate data for an increased signal for adverse side-  
291 effects.

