The primary clinical endpoint is the number of days required to reach a 50 percent reduction in the cumulative 0-36 score from the four symptom categories. For secondary endpoints we will assess a) the number of days required to reach a score of 0 b) total composite score at day 5 of the supplementation, c) differences in emergency room visits and d) differences in hospitalizations e) differences in severity of symptoms between study arms f) differences in number of patients who were prescribed adjunctive medications for their diagnosis, and g) differences in number of patients in study arms who experienced side effects from the supplements.

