### 246 **5.3 Secondary Endpoints**

247 Additional endpoints to be considered include:

248 A) Number of days required to reach a total score of 0

B) Individual severity of illness scores (fever, cough, shortness of breath, fatigue)

C) Cumulative severity score at day 5 of the study

D) Emergency room visits

E) Hospitalizations

F) Adjunctive prescribed medications

G) Side effects of supplementation

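### The side-effect endpoint counts only effects attributed to the supplements, so Arm D is zero by definition and its comparison with the active arms is not valid; the adverse-event recording rule depends on attribution too

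*Protocol*

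**What the plan says.** **The endpoint.** Protocol section 1.1, item g, is "differences in number of patients in study arms who experienced side effects from the supplements". Section 5.3, item G, shortens this to "Side effects of supplementation".

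**How it is collected.** Section 2.0 has staff call patients at days 7, 14, 21 and 28 and ask, among other things, about "any side effects from the study supplements that the patient could have experienced". In the same section Arm D (n=130) receives no study supplement. The schedule in section 4.1 marks side effects at days 7, 14 and 21 but not at day 28.

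**Adverse events.** Section 6.1.1 defines an adverse event "whether or not it is considered to have a causal relationship to the study drug, device or procedure". Section 6.1.3 then sets the recording rule: events "thought to be both serious, unexpected and related to study supplement(s) or procedures should be recorded in the database". The next sentence makes one exception: "All patient deaths; regardless of causality or relatedness should be recorded in the database". The section ends with "We will have a study safety committee to evaluate data for an increased signal"; it names neither the data nor the comparator.

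**What is collected without attribution.** Every arm is followed for vital status, hospitalizations and ER visits (sections 2.0, 4.1 and 5.1). Every arm also scores 12 symptoms daily from 0 to 3, including nausea, vomiting, diarrhea and headache (sections 1.1 and 2.0).

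**The concern.** A control arm shows how often a complaint occurs without the treatment. Here the question is worded so that a patient in Arm D cannot answer yes, so the background rate is never measured. The endpoint is nevertheless stated as a difference between arms.

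The overlap with the disease makes this more than a matter of form. Section 7.2 lists diarrhea, nausea/vomiting and headache among the supplements' effects, and these are also tracked COVID-19 symptoms. In an open-label trial, a patient with nausea in an active arm can blame the tablets, and the same nausea in Arm D is not a side effect. Attribution can also work the other way and hide a real effect by putting it down to the infection. An analysis of the attributed counts cannot undo either error.

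The recording rule in 6.1.3 has a related weakness. Relatedness and expectedness are judged by people who know the arm, and an event judged unrelated need not be kept as an adverse event at all, although 6.1.1 counts it as one.

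**Working it through.** **1. The plan's own figures.** The protocol gives no rate, power or test for side effects. Its only design figure is the primary-endpoint power, which reproduces: noncentrality = 4 × 130 × 0.188 / 3² = 10.86 on 3 and 516 degrees of freedom gives 79.5% against the stated 80%. It has no bearing on this point.

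**2. Listed effects (section 7.2) against what Arm D provides.**

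| Listed effect | In the 12-item daily tool? | Collected in Arm D? |
|---|---|---|
| Diarrhea, nausea/vomiting, headache | Yes | Yes, as symptoms, without attribution |
| Abdominal cramps, epigastric pain, decreased appetite, heartburn, flushing, tingling, numbness | No | No like-for-like question |

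So a control rate for the first row can be had from data already planned. For the second row it cannot.

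**3. Smallest count that looks significant against a fixed zero.** With x events in one active arm of 130 and 0/130 in Arm D, the two-sided Fisher p-value is 2 × C(130, x) / C(260, x).

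- x = 5: p = 0.060
- x = 6: p = 2 × 5.963×10⁹ / 4.048×10¹¹ = 0.029

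Six attributed events (6/130 = 4.6%) are therefore enough.

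**4. Chance of reaching six when the supplement does nothing.** Let q be the proportion of active-arm patients who attribute a complaint to the supplement although it has no effect, that is, the background rate times the fraction blamed on the tablets. The protocol gives neither quantity, so q is an assumption and is shown as a range. The chance is P(X ≥ 6) with X ~ Binomial(130, q).

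| Assumed q | Expected events (130q) | Chance of false significance |
|---|---|---|
| 1% | 1.3 | 0.2% |
| 2% | 2.6 | 4.7% |
| 2.5% | 3.25 | 10.9% |
| 5% | 6.5 | 63.7% |
| 10% | 13 | 99.2% |

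For example, q = 10% would arise from a 20% background rate with half of it blamed on the tablets; q = 2.5% from a 5% background with half blamed.

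**5. The same test with equal collection.** If both arms are asked the same question regardless of attribution and share a background rate, the type I error of the Fisher test is 0.9% at a 2% rate, 2.2% at 5%, 3.0% at 10%, 3.5% at 20% and 3.7% at 30%. It stays below the nominal 5% throughout.

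**6. Sections 6.1.1 and 6.1.3 side by side.** The definition disregards causality. The recording rule requires seriousness, unexpectedness and relatedness together, with deaths excepted. Section 6.1.2 classes inpatient hospitalization as serious, yet an admission judged unrelated or expected falls outside the required adverse-event record.

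**7. Day 28.** Sections 1.1 and 2.0 both have side effects asked at day 28. The section 4.1 row leaves that cell empty.

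**The case against.** A reader might infer that safety is counted only when attributed, that Arm D can have no event at all, and that the safety committee has no valid control. The documents do not support this. All deaths are recorded whatever their cause, and 6.1.3 also covers events related to study procedures, which can occur in Arm D. Vital status, admissions, ER visits and the daily nausea, vomiting, diarrhea and headache scores exist by arm without attribution. Hospitalizations and ER visits are themselves secondary endpoints, so an excess of admissions judged unrelated would still be visible there. Nothing limits the committee to events that pass the 6.1.3 filter; its data set is unstated, which is not the same as restricted.

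Three further objections carry weight. Section 6.1.3 does not forbid recording other events, and its sentence joins recording with IRB reporting; non-serious side effects are also gathered on the calls. Section 5.4 names a test only for the primary endpoint, so no Fisher test of endpoint g is planned here, and the SAP is not at hand. The false-positive figures depend wholly on the assumed attributed rate: at 2% or below they do not exceed 5%. Section 7.2 puts vitamin C's diarrhea, nausea/vomiting and headache effects below 1%, although that is not a rate at which COVID-19 patients blame the tablets.

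None of this removes the structural zero. It comes from the definition of the endpoint and the wording of the question, and an SAP cannot recover answers that were never sought in Arm D. Comparisons among the three active arms remain possible, though open-label attribution can bias them.

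**Conclusion.** The point holds in this limited form. Endpoint g has no like-for-like control, because Arm D is zero by definition for supplement-attributed effects. The listed effects outside the 12-item tool are not collected in Arm D. The recording rule in 6.1.3 is at odds with the definition in 6.1.1, and the day-28 entries disagree.

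If endpoint g were tested against Arm D as worded, the chance of a false finding of harm would run from negligible to near certain over assumed attributed rates of 1% to 10%, passing 5% just above a 2% rate. This assumes 130 evaluable patients per arm, a two-sided Fisher test at 0.05 and no true effect. The structural zero itself needs no assumption.

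The defect concerns one secondary endpoint and the adverse-event record. It does not affect the primary endpoint or the comparisons of deaths, admissions and ER visits. It should be corrected, because the correction is cheap and mostly uses data already planned.

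**What to change.** 1. **Redefine endpoint g** (sections 1.1 and 5.3) as the number of patients per arm with at least one complaint from a prespecified list, new or worsened from baseline within a fixed window such as the supplementation period, asked identically in all four arms regardless of attribution. Take nausea, vomiting, diarrhea and headache from the daily tool, and the remaining listed effects from a short checklist on the existing calls. Keep both list and window closed: an open category for any complaint over 28 days could be met by most symptomatic patients in every arm and leave nothing to compare. Since the daily tool is not required after admission, state how admitted patients are counted.
2. **Report attributed side effects** descriptively, in the three active arms only.
3. **In 6.1.3**, record serious adverse events in all arms irrespective of relatedness or expectedness, and state that the safety committee receives counts by arm. IRB reporting can stay as written.
4. **Reconcile day 28** between sections 1.1 and 2.0 and the schedule in 4.1.

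The cost is revised wording, one checklist form and slightly more data entry. Deaths, admissions, ER visits and the overlapping symptoms are already collected.

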(none of these additional supplements). These supplements will be given to patients for a duration of ten days as a part of the study. Patients will be asked to track their symptoms of systemic illness on a daily basis.(Appendix A: Symptom Assessment Tool). We will track 12 symptoms on a scale of 0-3 as follows: A) Temperature Scale (if patient has a thermometer): 0 =  $\leq 98.6$ , 1 =  $> 98.6 - 100.6$ , 2 =  $> 100.6 - 102.6$ , 3 =  $> 102.6$ ; If no thermometer: 0= No fever & no chills, 1= No fever & chills, 2= Fever & no chills, 3= Fever & chills B) Cough Scale: 0 = no cough, 1 = mild, 2 = moderate, 3 = severe C) Shortness of breath: 0 = no shortness of breath, 1 = with moderate intensity exercise 2 = with walking on flat surface 3 = short of breath with getting dressed or daily activities D) Fatigue: 0 = No fatigue/energetic, 1=mild fatigue, 2=moderate fatigue, 3=severe fatigue E) Muscle or body aches: 0 = No muscle or body aches, 1=mild muscle or body aches, 2=moderate muscle or body aches, 3=severe muscle or body aches. F) Headache: 0 = No headache, 1=mild headache, 2=moderate headache, 3=severe headache G) New loss of taste: 0 = No loss of taste, 1=mild loss of taste, 2=moderate loss of taste, 3=severe loss of taste H) New loss of smell: 0 = No loss of smell, 1=mild loss of smell, 2=moderate loss of smell, 3=severe loss of smell I) Congestion or runny nose: 0 = No congestion or runny nose, 1=mild congestion or runny nose, 2=moderate congestion or runny nose, 3=severe congestion or runny nose J) Nausea: 0 = No nausea, 1=mild nausea, 2=moderate nausea, 3=severe nausea K) Vomiting: 0 = No vomiting, 1=mild vomiting, 2=moderate vomiting, 3=severe vomiting L) Diarrhea: 0 = No diarrhea, 1=mild diarrhea, 2=moderate diarrhea, 3=severe diarrhea. Each patient will have a composite score ranging from 0-12/day. The tracking will continue for the 28 days of study participation for each subject. They will also be asked to complete a questionnaire at the beginning of study period, day 7, day 14, day 21 and day 28. The purpose of the

questionnaire is to assess whether patient received additional medications/ supplements, sought treatment at emergency rooms or were hospitalized, or experienced side effects from the study supplements.

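### Section 6.1.3 applies the IRB-reporting filter to database recording as well, so non-fatal serious events judged expected or unrelated need no adverse-event entry

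*Protocol*

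**What the plan says.** Section 6.1.1 of the protocol defines an adverse event as an untoward occurrence "whether or not it is considered to have a causal relationship to the study drug, device or procedure". Section 6.1.2 defines seriousness by outcome alone and lists five outcomes, among them "Inpatient hospitalization"; it adds important medical events as a matter of medical judgement.

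Section 6.1.3 then narrows what is documented. Events that the investigator considers "thought to be both serious, unexpected and related to study supplement(s) or procedures should be recorded in the database and reported to the IRB". The next sentence makes one exception: "All patient deaths; regardless of causality or relatedness should be recorded in the database". The same section sets up a safety committee to look for a signal of adverse side effects, without saying which data it receives.

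Other sections collect safety information by a different route. Under section 2.0, "Study team members will call patients at days 7, 14, 21, and day 28 of the study period" and ask about hospitalizations, ER visits, added medications and supplement side effects. Section 1.1 describes a questionnaire on whether patients "sought treatment at emergency rooms or were hospitalized, or experienced side effects from the study supplements". The secondary endpoints in the same section include "c) differences in emergency room visits and d) differences in hospitalizations", and section 5.3 lists both again. The section 4.1 schedule adds vital status at day 28.

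**The concern.** Which events go promptly to an ethics board and which events are written down as adverse events are separate questions. The first is properly restricted to serious, unexpected and related events. The second is not, because causality is easier to assess once events have been collected without regard to presumed cause. Section 6.1.3 answers both with the same restriction.

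Two features of this trial make the restriction less comfortable. Treatment is open label, so the investigator knows the arm when judging relatedness. And the rule does not work evenly across arms. For the control group the protocol says "Patients in Arm D (n=130) will not receive any of the study medications and continue on standard of care", so no event there can be related to a supplement, and only study procedures could bring a non-fatal event through the filter. Non-fatal adverse-event entries would come almost entirely from Arms A to C.

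At stake is whether the safety committee has a uniform record of serious events, each with a stated attribution, or admission counts with attribution required for only some of them.

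**Working it through.** The protocol gives no figure to reproduce here. The check is to apply section 6.1.3 case by case, then see what the other sections collect.

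**Applying the rule**

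| Event | Entry required by 6.1.3? | Collected elsewhere? |
|---|---|---|
| Death | Yes | Vital status at day 28 |
| Non-fatal, serious, unexpected, related | Yes | Admission, ER visit or side effect, if on the calls |
| Non-fatal, serious, related but expected | No | As above |
| Non-fatal, serious, judged unrelated | No | Only if there was an admission or ER visit |
| Non-serious | No | Only as a supplement side effect or a diary symptom |

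The sentence on deaths supports this reading. If serious events were recorded whatever their cause, deaths would need no exception for recording. The rule is a minimum and does not forbid further entries, but no other section requires an adverse-event entry, or a judgement of relatedness and expectedness, for rows three and four.

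**Which serious outcomes could leave no record at all**

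Section 6.1.2 lists 5 outcomes.

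- Death is exempt from the filter: 5 − 1 = 4.
- Hospitalization is asked about at 4 of 4 calls in every arm: 4 − 1 = 3.
- Congenital anomaly is scarcely relevant with pregnancy excluded and 28 days of follow-up: 3 − 1 = 2.

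The 2 left are a life-threatening experience and lasting disability, plus important medical events. They escape only when there is also no admission, no ER visit and no reported side effect. The side-effect question is worded in sections 1.1 and 2.0 as effects of the study supplements, which read literally does not apply in Arm D.

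**How many admissions could lack a required attribution**

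The protocol gives no admission rate, so a range is assumed:

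- at 2%: 520 × 0.02 = 10.4 admissions, or 10.4 / 4 = 2.6 per arm;
- at 10%: 520 × 0.10 = 52 admissions, or 52 / 4 = 13 per arm.

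These are upper limits for admissions at each rate, because they treat every admission as non-fatal and outside the filter. They exclude the serious events without admission described above.

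**A related mismatch in the schedule**

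Sections 1.1 and 2.0 ask about side effects at days 7, 14, 21 and 28. The Side Effects row in section 4.1 is marked at days 7, 14 and 21, which is 3 of the 4 calls.

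**The case against.** The best defence is that sections 6.1.1 and 6.1.2 only define terms, while section 6.1.3 deliberately narrows documentation for a study described in section 7.2 as minimal risk, with over-the-counter supplements taken for 10 days. On this view there is no contradiction, only a preference for fuller recording. The comparison that matters in an open-label trial is all-cause events by arm, and hospitalizations and ER visits supply it. An expected and related event would be a supplement side effect, which is asked about on the calls and is a secondary endpoint, so attribution is partly captured already. Applying the filter also means that the investigator considers relatedness and expectedness; only the negative answer need not be written down. The questionnaire is not shown and may ask for cause.

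Most of this stands, and it limits the size of the point. Kidney stones show how. Section 7.2 lists them for vitamin C at 6000 to 8000 mg, and Arms A and C take 8000 mg daily. But it ties them to prolonged use, so a stone in a 10-day course might well be judged unexpected and then be recorded. If it were judged expected, the admission would be counted but no entry would be required. Such cases should be rare, since a history of calcium oxalate stones is an exclusion. It is also true that a relatedness judgement carries little information in Arm D.

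The defence does not supply the missing requirement. No section attaches a judgement of cause or expectedness to the admission counts. An unwritten negative judgement cannot be reviewed by the committee. The alternative costs very little.

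**Conclusion.** The concern holds, and it is minor. As written, section 6.1.3 requires adverse-event entries only for deaths and for serious, unexpected and related events, which gives a selective record that differs between the supplement arms and Arm D. The planned comparisons of hospitalizations and ER visits are not affected, and the risk to participants is limited.

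The loss has two parts: a required attribution for non-fatal serious events judged expected or unrelated, and any required record of the rare serious event that comes with no admission, ER visit or reported side effect. The reading of the text rests on no assumption. The counts of about 10 to 52 admissions rest on the assumed 2% to 10% range and show scale only. If the questionnaire or case report forms already ask for cause, the practical loss is smaller still.

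**What to change.** Reword section 6.1.3 so that all serious adverse events as defined in section 6.1.2 are recorded in the database in all four arms, with the investigator's judgement of relatedness and expectedness. Keep IRB reporting as it is: serious, unexpected and related events, and all deaths, under current policy. As a minor correction, mark Side Effects at day 28 in the section 4.1 schedule so that it agrees with sections 1.1 and 2.0.

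The cost is a short amendment plus one entry per serious event, mostly admissions already asked about on the calls. At an assumed 15 to 30 minutes each, the range runs from 10.4 × 15 = 156 minutes (2.6 hours) to 52 × 30 = 1,560 minutes (26 hours) over the whole trial. The drawback is that most of this time goes on events that will be judged unrelated.
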